### Knowledge Gaps

In summary, the prevalence of extreme obesity has increased dramatically and bariatric surgery is the most effective treatment available. However, access to bariatric care in Canada is severely limited and wait times are lengthy. The ramifications of protracted wait times on health and health care costs have not previously been examined. In addition, data assessing the clinical and cost effectiveness of surgery in Canada are limited and further study is needed. Specifically, a comprehensive, population-based prospective assessment of the economic consequences from a health care payor, public payor (health care + other benefits such as unemployment insurance and other transfer payments), and societal (public payor, out-of-pocket costs, home and work productivity costs) perspective has not been performed to our knowledge in Canada or elsewhere.

Lastly, much of the prospective data evaluating bariatric procedures comes from the SOS study. However, vertical banded gastroplasty, which is now outdated, comprised nearly 70% of the procedures performed in SOS. More recent studies have evaluated gastric banding and gastric bypass and have reported similar results to SOS in terms of weight reduction and improvement in obesity-related comorbidities [44,45]. However, no prior studies comparing sleeve gastrectomy to medical management and APPLES results will help address this knowledge gap.

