### Data Collection and Outcome Measures (Additional File 1 and Table 1)

**Table 1 T1:** Cost categories and details of source data for quantification and valuation of relevant costs

**Cost Category**^**1**^	Source Details	Units of Resources	Time Frame
1. Inpatient encounters	Administrative data	# of hospitalizations length-of-stay	Provided by fiscal year Referenced to time zero
2. Outpatient encounters	Administrative data	# encounters # procedures	Provided by fiscal year Referenced to time zero
3. Physician Fees	Administrative data	# encounters Provider specialty Service provided	Provided by fiscal year Referenced to time zero
4. Medications	Patient interview	Name Dosage, frequency & duration	Bi-annual
5. Weight Wise Clinic Visits	Administrative data and chart review	Personnel (nurses, dieticians, support staff) salaries Administrative and capital costs Supplies & equipment	Provided by fiscal year Referenced to time zero
6. Home Care & Long Term Care	Patient interview	Personnel (nurse, OT, PT, RT) salaries Disability aids (walker, bars, rails, etc.) Administrative and capital costs	Bi-annual
7. Transfer Payments	Patient interview	Unemployment insurance Disability benefits Assured Income for the Severely Handicapped (AISH)	Bi-annual
8. Employment status, absenteeism	Patient interview	Employment status in past year (# hours/week, # weeks) Absenteeism in past year (# days) Annual income (by quintile)	Bi-annual
9. Weight Loss Interventions	Patient interview	Weight loss program, meal replacements, physical trainer, exercise programs, alternative therapies, nutritional counselling, commercial program	Bi-annual
10. Mobility and Medical	Patient interview	Mobility aids, home modification/renovations, rehabilitation, paid personal assistance (household activities and home productivity, driving)	Bi-annual
11. Personal/Household Productivity	Patient interview as part of quality of life surveys	Capacity to perform household/domestic activities, personal care, and participate in leisure activities (Scalar) Paid/unpaid caregivers	Bi-annual

AHCIP = Alberta Health Care Insurance Plan. MACAR = Morbidity and Ambulatory Care Abstracting Record. DAD = Discharge Abstract Database. LOS = Length of stay. CIHI = Canadian Institute for Health Information. OT = occupational therapy. PT = physiotherapy. RT = respiratory therapy. SW = social worker.

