^1^Health Care Payor perspective includes cost categories 1-6; Public Payor perspective includes cost categories 1-7 and Societal Payor perspective includes all costs.

After informed consent is obtained, baseline data collection for consenting patients will include the following: age, sex, race, marital status, employment status, household income quintile (≤ 20 K, 20-40 K, 40-60 K, 60-80 K, ≥80 K), general medical history and obesity-related comorbidities, smoking status (current, past, never), detailed current and past medications, weight, BMI, waist circumference, blood pressure, fasting lipids, fasting glucose, HbA1c, and liver enzymes.

Body weight will be measured using a validated, calibrated scale to the nearest 0.1 kilogram after the patient has emptied his/her bladder. Subjects will wear light indoor clothing with empty pockets and no shoes. Height will be measured using a wall-mounted stadiometre. A single reading taken using an automated blood pressure monitor and using an appropriately sized blood pressure cuff will be recorded with the subject seated in a chair and after five minutes of rest.

Repeat assessment of blood pressure, body weight, and cardiovascular risk factors (cholesterol profile, glycemic parameters) will be performed at 2 years.

Additional outcomes to be collected every 6 months will include:

1. **Household income and employment status**

2. **Quality of life and utility measurement**: Health related quality of life will be measured using validated, widely-used instruments. Generic and preference-based quality of life will be assessed using the Short Form-12 (SF-12[50]) and the EuroQol-5D (EQ-5D[51]) respectively. Obesity-specific quality of life will be assessed using the Impact of Weight on Quality of Life-Lite (IWQOL-Lite) [52].

3. **Patient satisfaction: **Satisfaction with medical care will be assessed using two questions, which will be rated on a 5-point Likert Scale:

a. The medical care I have been receiving is just about perfect

b. I am dissatisfied with some things about the medical care I received.

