b. **Patient-Reported: **Second, in order to comprehensively capture all economic consequences and enable a societal perspective, each patient enrolled in the study will provide additional information retrospectively for the year prior to enrolment and prospectively for two years after enrolment on a bi-annual basis. Resource use will be identified through investigator and clinical experience as well as examination of comprehensive costs lists, and published literature (Table 1) [57]. There is no previously validated data collection instrument to measure these costs in obesity; thus, we have developed a comprehensive instrument using commonly used techniques [58,59]. Societal costs include costs of weight loss interventions (meal replacement, weight loss programs, alternative therapy, medications), mobility and medical costs (mobility aids, home modifications, rehabilitation, home care, housekeeping), workforce productivity (employment, absenteeism), home productivity (domestic chores, leisure activity, use of paid or unpaid caregivers) and transfer payments (unemployment insurance), and will be valued in accordance with Canadian guidelines [60].

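### The societal cost total includes transfer payments, which are not a societal resource cost and can count the same work loss twice

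*Protocol article*

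**What the plan says.** Table 1 of the protocol article numbers eleven cost categories. Category 7, transfer payments, consists of "Unemployment insurance Disability benefits Assured Income for the Severely Handicapped (AISH"). Category 8 records work: "Employment status in past year (# hours/week, # weeks) Absenteeism in past year (# days"), together with income.

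Three places put both into the societal total:

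- **Table 1, footnote 1:** "Public Payor perspective includes cost categories 1-7 and Societal Payor perspective includes all costs".
- **Economic Data, patient-reported paragraph:** the list of societal costs includes "workforce productivity (employment, absenteeism), home productivity (domestic chores, leisure activity, use of paid or unpaid caregivers) and transfer payments (unemployment insurance").
- **Knowledge Gaps:** the perspective is defined as "societal (public payor, out-of-pocket costs, home and work productivity costs"). The same sentence defines the public payor view as health care plus benefits and other transfer payments.

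The only valuation rule is a general reference at the end of the list of societal costs: "use of paid or unpaid caregivers) and transfer payments (unemployment insurance), and will be valued in accordance with Canadian guidelines". No rule removes transfers from the societal sum or nets them against lost work.

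**The concern.** A benefit paid from public funds to a patient is a loss to the payer and an equal gain to the recipient. Across society the two cancel and no resource is used. The resource lost when someone cannot work is the work itself, which is what category 8 is there to capture. A societal total that also contains category 7 includes an item that is not a societal cost, and it may enter the same loss twice.

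Objective 3 is exposed to this. It predicts that savings outside direct health care will outweigh the higher direct cost of surgery. If surgical patients draw fewer benefits, including category 7 enlarges the societal saving in the direction of that prediction. The costs are then fed into the model of raising surgery rates from 0.1% to as much as 10% of eligible patients, whose societal version would inherit the error.

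**Working it through.** The documents give no benefit or wage amounts, so there is no figure of the plan's own to reproduce. The check is of definitions, followed by algebra and an illustration on assumed amounts.

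**1. Composition of the totals.** Let c1 to c11 be the cost categories.

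- Public payor = c1 + ... + c7. Transfers belong here.
- Societal as written = c1 + ... + c11.
- Societal resource cost = (c1 + ... + c6) + (c8 + ... + c11).
- Excess = c7.

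The error in a comparison of mean societal cost between arms is the difference between arms in mean c7. Its sign follows benefit receipt: fewer benefits in the surgical arm inflate the saving, and more benefits would shrink it.

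**2. Where the double count arises.** Let W be the value of work lost in a spell, and let a benefit replace share r of it. If category 8 prices that spell at W, the plan enters W + rW although the societal loss is W. For an assumed W = $10,000:

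| Assumed r | Entered, W(1 + r) | Societal loss |
|---|---|---|
| 25% | $12,500 | $10,000 |
| 50% | $15,000 | $10,000 |
| 75% | $17,500 | $10,000 |

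These are overstatements of the work-loss component of a benefit recipient, not of total societal cost.

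**3. Illustration of the effect on an arm comparison.** Error per patient = (difference in proportion receiving benefits) × (benefit per recipient-year) × (years). All three inputs are assumed: 5 percentage points, $10,000 to $20,000, and two full years.

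- 0.05 × $10,000 × 2 = $1,000
- 0.05 × $20,000 × 2 = $2,000

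**4. Possible overlaps between other categories.**

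- Category 6 lists "Disability aids (walker, bars, rails, etc".); category 10 lists "Mobility aids, home modification/renovations, rehabilitation, paid personal assistance (household activities and home productivity, driving").
- Category 11 lists paid and unpaid caregivers, next to the paid personal assistance in category 10.
- Home care is in category 6 of Table 1, but the patient-reported paragraph groups it with mobility and medical costs, which is category 10.
- Medications are category 4 of Table 1, but that paragraph groups them with weight loss interventions, which is category 9.

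Each is a difference or closeness of labels. None by itself shows that an amount is added twice.

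**The case against.** **The guideline reference may deal with it.** Valuation follows Canadian guidelines, which are not among the documents. But the sentence that cites them names transfer payments as a societal cost, and the footnote includes every category. A general reference does not take out an item that the text puts in.

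**Counting twice is not certain.** This stands in part. The article does not say how category 8 is priced. For someone long out of work on AISH, category 8 might carry little or no cost, and then nothing is counted twice. The transfer would still not be a societal resource cost, so the total would still be wrong.

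**The effect is contained.** Costs are to be described by perspective and category, so category 7 will be visible. The Discussion ties its example of surgery being dominant to the public payor view, where transfers belong. Both points stand and limit the consequences. Subtraction afterwards is only a partial remedy, however: it works for arithmetic means, but not for medians or for results from log-transformed totals, both of which the plan allows for.

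**The overlaps may be deliberate.** A reader might infer from the similar labels that aids, paid help and home care are each summed twice. The documents do not show this. Category 6 enters the health care payor total and category 10 only the societal one, so payer-borne aids in one and patient-bought aids in the other is a natural reading. Home care appears only once in Table 1. The collection instrument, which would settle the matter, is not shown.

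**Conclusion.** The societal total is wrong as defined. It includes transfer payments in three mutually consistent places, and nothing in the article removes them. Where category 8 values the same spell off work, the loss is counted twice. The direction favours the objective 3 hypothesis if surgery reduces benefit receipt. This point leaves the health care payor and public payor totals untouched.

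The size cannot be taken from the documents. The $1,000 to $2,000 per patient rests wholly on assumed inputs and shows only that the error need not be trivial. Two stronger readings should be avoided:

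- **Setting that range against the detectable cost difference.** The sample size text implies 0.20 × $12,183 = $2,437, but it does not say which perspective the $12,183 represents. The comparison would lend the range weight it does not have.
- **Quoting a percentage overstatement of societal cost.** An assumed $15,000 benefit against $40,000 of lost wages gives 15,000 / 40,000 = 37.5%, but that is one recipient's work-loss component. As a share of total societal cost it is smaller, and smaller again averaged over an arm that includes non-recipients.

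The category overlaps are a secondary matter: a risk to rule out, not a shown error.

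**What to change.** 1. Reword footnote 1 of Table 1 so that the societal perspective is categories 1-6 and 8-11, with category 7 kept in the public payor total.
2. Bring the other two places into line: the societal definition in Knowledge Gaps, which is built on public payor costs, should exclude transfer payments, and the list of societal costs in the patient-reported paragraph should no longer name them. Changing the footnote alone would leave the text contradicting itself.
3. Use the same definition in the cost regressions and in the societal version of the model of higher surgery rates.
4. Confirm against the collection instrument that paid assistance (category 10) and paid caregivers (category 11), and disability aids (category 6) and mobility aids (category 10), are each priced once.
5. Reconcile the placement of home care and medications between Table 1 and the text. This decides which perspective they enter: categories 4 and 6 count for the health care payor, categories 9 and 10 only for society.

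The cost is wording and a changed sum in the analysis. Category 7 is collected anyway for the public payor view, and no extra data are needed.

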### Statistical Analysis and Sample Size Considerations

#### Clinical, Humanistic and Economic Outcomes in Wait-listed Patients

This analysis specifically focuses on the wait-listed group and will examine two-year change scores in each relevant outcome using the appropriate statistical methodology. Analyses will be conducted in all wait-listed patients as well as those indicating a specific interest in surgery. Examples of clinical outcomes include anthropometric indices, blood pressure, lipid profile, glycemic control, diabetes prevalence. Examples of humanistic outcomes include QOL and patient satisfaction. Economic outcomes include total and categorical costs. For example, two-year change scores will be analysed for QOL domains (e.g. SF-12, IWQoL-Lite) using appropriately calibrated and constructed linear regression models and/or analysis of variance. Because these are self-reported data collected on a semi-annual basis, we will use a "last-value carried forward" approach to handle missing data as our primary analytic strategy.

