## Objectives and Hypotheses

The APPLES study is a population-based, prospective controlled study enrolling at minimum of 500 patients and designed to assess the impact of extended wait-times for bariatric care and examine the clinical and cost-effectiveness of bariatric treatment in the Canadian context.

The three major objectives of APPLES are:

1. To assess the impact of extended wait times for bariatric care by examining the two-year change in clinical, economic and humanistic outcomes in wait-listed patients. We hypothesize that patients will report progressive deterioration in these outcomes over time.

2. To determine the clinical effectiveness and changes in health-related quality of life associated with modern bariatric procedures and compare these outcomes to medically treated controls and untreated wait-listed controls. We hypothesize that surgery will markedly reduce body weight, decrease the need for unplanned medical care, and increase quality of life compared to controls.

3. To compare the costs associated with bariatric surgery to costs associated with medical and wait-listed controls over three years, from societal, public payor, and health care payor perspectives. We hypothesize that lower indirect, out of pocket and productivity costs will offset increased direct health-care costs resulting in lower total costs for bariatric surgery.

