## Methods/design

### Overall Study Design

In this prospective cohort study, consecutive and consenting patients enrolled in the Weight Wise Regional Obesity Program and without a contraindication to surgery will be enrolled. The minimum enrolment sample size will include 150 surgical patients, 200 patients receiving intensive medical therapy and 150 patients wait-listed to enter the clinic (Figure 1). The number of patients enrolled in the medical arm is larger because we anticipate an increased rate of censoring in this study arm, as some of these patients will ultimately undergo bariatric surgery within the two-year follow-up period.

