### Study Setting and Subject Recruitment

The Edmonton Weight Wise program is a comprehensive initiative established in 2005 designed to deliver integrated, patient-focused, evidence-based care to the Edmonton Zone of Alberta Health Services (AHS). This region is one of the largest integrated health delivery systems in Canada and includes a catchment population of approximately 1 million residents within greater Edmonton and an additional 600 000 residents in surrounding regions cared for by more than 1000 physicians, with an annual healthcare budget of almost two billion dollars [46].

Weight Wise includes a central, region-wide single-point-of-access referral system; community education and weight management sessions; and adult and pediatric bariatric specialty clinics. Adult specialty services are offered to patients with BMI levels of ≥ 35 kg/m^2 ^referred from a medical practitioner. By extrapolating from contemporary Canadian obesity surveillance data (i.e. ~8% of Canadians are moderately [BMI 35.0-39.9 kg/m^2^] or severely [> 40 kg/m^2^] obese), we estimate that over 125 000 adult patients within our region's catchment area has a BMI ≥ 35 kg/m^2 ^[6]. Community-dwelling patients referred for evaluation in the adult clinic are wait-listed at the time of referral (Figure 2). Currently, over 2000 adult patients are wait-listed for entry into the specialty clinic and their average wait may be up to several years in duration. Wait-listed patients are expected to attend community-based group education sessions prior to clinic entry. Otherwise, they receive no specific intervention.

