### Eligibility For Surgery

Within the adult specialty clinic, patients receive approximately 24-36 weeks of intensive lifestyle counselling (diet, exercise, behavioural modification), delivered by a multidisciplinary staff (internists, dieticians, nurses, physiotherapists, and psychologists) according to current recommendations [14]. Patients are seen approximately every 4-8 weeks. Patients interested in bariatric surgery are also evaluated for this procedure by the same multidisciplinary staff. Patients deemed to be appropriate candidates are subsequently evaluated by a bariatric surgeon. Patients with BMI levels ≥ 35-39.9 kg/m^2 ^and a major medical comorbidity (e.g., hypertension, type 2 diabetes, sleep apnea) or BMI levels ≥ 40 kg/m^2 ^are considered potential candidates for surgery. Absolute contraindications to surgery include pregnancy, uncontrolled psychiatric disease, active substance abuse or smoking (patients are required to quit prior to surgery), an active eating disorder (anorexia or bulimia), and high-risk for surgery medical status (e.g. severe coronary artery disease). Because of limited data documenting the benefits of surgery in patients younger than 18 years of age and evidence for possible harm in patients over 60,[47] procedures are not performed in these age groups. In order to access surgery, patients are also required to demonstrate commitment to attend scheduled appointments and adhere to lifestyle modification and behavioural therapy.

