#### Comparing Clinical and Humanistic Outcomes in Patients Treated with Surgery to Medically Treated and Wait-listed Patients

Outcomes are similar to those listed above. Two-year mean changes in continuous variables will be compared between the surgical arm and medical or wait-listed controls using unpaired t-tests for continuous outcomes and chi-squared tests for dichotomous ones. Multivariable predictors of the 2-year change in a given outcome will be identified using appropriately constructed and calibrated covariate-adjusted linear regression models for continuous outcomes or logistic regression models for dichotomous ones. Patients who cross over to another study arm (e.g., medically treated patients who undergo surgery) will be censored at the point of cross over and a last-observation-carried-forward approach to missing data will be used for the primary analysis.

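### Objective 1 states no rule for wait-listed patients who enter the clinic within two years, and either available reading can bias the estimated effect of waiting toward no change

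*Protocol article*

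**What the plan says.** The first objective (Protocol article, Objectives and Hypotheses) is "To assess the impact of extended wait times for bariatric care by examining the two-year change in clinical, economic and humanistic outcomes in wait-listed patients", and the hypothesis is progressive deterioration. Overall Study Design describes this group as 150 patients waiting to enter the clinic. Study Setting and Subject Recruitment says that "their average wait may be up to several years in duration". It adds that these patients are expected to attend community group education and that "Otherwise, they receive no specific intervention". After clinic entry, "patients receive approximately 24-36 weeks of intensive lifestyle counselling", and those interested in surgery are assessed for it (Eligibility For Surgery).

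The Objective 1 analysis section takes two-year change scores as the outcome and states: "Analyses will be conducted in all wait-listed patients as well as those indicating a specific interest in surgery". On missing values it says "we will use a 'last-value carried forward' approach to handle missing data as our primary analytic strategy". It gives no rule for clinic entry.

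The only crossover rule stands in the section comparing surgery with the two control groups: "Patients who cross over to another study arm (e.g., medically treated patients who undergo surgery) will be censored at the point of cross over", followed by last observation carried forward. Overall Study Design mentions crossover only for the medical arm: "some of these patients will ultimately undergo bariatric surgery within the two-year follow-up period".

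Under Data Collection and Outcome Measures, quality of life is collected every 6 months. Weight, blood pressure, lipids and glycaemic measures are repeated only at 2 years.

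**The concern.** Clinic entry ends the exposure that Objective 1 is meant to study. On the list a patient gets little beyond group education. In the clinic the same patient gets months of intensive counselling and possibly an operation. A two-year change over everyone who began on the list measures the effect of waiting only if nobody is admitted, or if admission is handled explicitly. The section fixes the population, the outcome and the missing-data rule, but not the event that ends waiting.

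The Discussion says the study will help decision makers judge whether current waits worsen health. An estimate pulled toward no change could make waiting look less harmful than it is.

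**Working it through.** **Inputs from the Protocol article.** 150 wait-listed patients, SF-12 SD 9, important change 5 points, IWQoL-Lite SD 18.7, important change 10 points, two-sided alpha 0.05, 30% attrition. The stated beta of 0.90 is read as power. **Assumptions, not in the document:** share f admitted within 24 months, and the entrants' change g.

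**1. The plan's own figures.** For a one-sample t-test of mean change, with the stated SD taken as the SD of change, n = 37 (SF-12) and 39 (IWQoL-Lite). Multiplying by 1.3 gives 48.1 and 50.7, which match the stated 48 and 51. These sample sizes contain no allowance for clinic entry.

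**2. Reading A: the crossover rule does not apply to Objective 1.** A value measured after entry is not missing, so it is used. For a true on-list SF-12 change of -5,

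mean = (1 - f)(-5) + f·g.

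Power uses n = 150 × 0.7 = 105 and mixture SD = √[81 + f(1 - f)(5 + g)²], by normal approximation.

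| f | mean, g = 0 | power | mean, g = +5 | power |
|---|---|---|---|---|
| 0 | -5.0 | >0.99 | -5.0 | >0.99 |
| 10% | -4.5 | >0.99 | -4.0 | 0.99 |
| 20% | -4.0 | 0.99 | -3.0 | 0.88 |
| 30% | -3.5 | 0.97 | -2.0 | 0.53 |

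For example, at f = 30% and g = +5: 0.7(-5) + 0.3(5) = -2.0; SD = √(81 + 21) = 10.1; SE = 10.1/√105 = 0.99.

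IWQoL-Lite behaves in the same way. With a true 10-point decline and entrants gaining 10, power is 0.99, 0.86 and 0.50 at 10, 20 and 30%.

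**3. Reading B: the crossover rule applies, with carry-forward.**
- *6-monthly outcomes.* With linear decline, a patient admitted at month 12 carries forward half of the two-year change, -2.5. At f = 30% the mean is 0.7(-5) + 0.3(-2.5) = -4.25; at 10% it is 0.9(-5) + 0.1(-2.5) = -4.75.
- *Measures taken only at baseline and 2 years.* The last study value before entry is the baseline value, so the carried change is exactly zero. The mean is (1 - f) times the true change: 10% of any deterioration is lost at f = 10%, and 30% at f = 30%.

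**4. Ending the analysis at clinic entry.** If entry is unrelated to outcome, using only patients still waiting keeps the mean at -5. At f = 30%, n = 73.5, SE = 9/√73.5 = 1.05 and power is above 0.99. At f = 40%, n = 63 and power is still 0.99.

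**The case against.** The strongest reply is that the crossover rule is worded generally. Medical-to-surgical crossover is given only as an example, a wait-listed patient who starts clinic treatment also changes arm, and the same 150 patients are governed by the rule in Objective 2. Overall Study Design expects a higher rate of censoring in the medical arm, which suggests some censoring elsewhere. The article is also a condensed account, and the reach of a rule may be settled in the full protocol.

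This stands in part. A reader might infer that the plan counts treated patients as still waiting. The document does not say so; the Objective 1 section is silent. But extending the rule does not remove the problem, because the carry-forward attached to it produces the losses in step 3.

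It is also fair that waits are long. The Background cites a 5-year average for publicly funded procedures in Canada, so f may be small.

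A reader might further infer that the 33% surgical weight loss cited in the article would swamp any gain on the list. The documents do not support this. That figure applies at 2 years or later. With at least 24 weeks of counselling first, a patient admitted on day 1 has about 18 months after surgery at most, and no share operated on is given. With the Background's 3-5% loss for lifestyle treatment and an assumed 3% on-list gain, 30% admitted gives 0.7(3) - 0.3(5) = +0.6%, and 10% gives 0.9(3) - 0.1(5) = +2.2%. The gain is diluted, not reversed.

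**Conclusion.** The point holds as a gap with a probable direction and an unknown size. The Objective 1 section does not say how clinic entry is handled, and neither available reading gives the change due to waiting. If waiting is harmful and entrants do no worse than those still waiting, both readings shrink the estimate. That condition may fail for costs, since clinic visits are themselves a cost category in Table 1.

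It does not follow that deterioration will be hidden. At 10% admitted, SF-12 power stays at 0.99 or above under both values of g. At 30% admitted with no net change in entrants it is 0.97. A serious loss of power needs both substantial admission and a strong response, and the document gives neither. With nobody admitted there is no bias.

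The change is worth making because it is cheap and serves the study's first objective.

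**What to change.** - State whether the crossover rule under Objective 2 applies to Objective 1, and reconcile the two sections.
- Record the clinic-entry date for every wait-listed patient.
- Define the primary Objective 1 analysis on time spent on the list, ending at clinic entry.
- For 6-monthly outcomes, replace carry-forward with a longitudinal mixed model of the on-list visits.
- For measures taken only at baseline and 2 years, do not carry baseline forward for admitted patients. Analyse those still waiting at 2 years, and add clinic-entry chart values, with time since baseline in the model, only where they are available.
- Report the all-patient two-year change as secondary, with the numbers admitted and operated on.

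The cost is revised analysis text, one date per patient and some chart abstraction. Table 1 lists chart review only for costing clinic visits, so study-grade entry measurements cannot be assumed. There will be somewhat fewer on-list observations at 24 months. The mixed model assumes that entry is ignorable given the observed data. The comparison limited to patients still waiting rests on a similar assumption, which should be stated.
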